**Figure 1 figure1:**
[figure not shown]
Flow diagram of study design.

**Table 1 table1:** Age-appropriate safety counseling topics adopted and modified based on The Injury Prevention Program (TIPP).

Age	Safety counseling topics
1.5 to 2 months	
	Falls
	Scalds
	Sleeping safety
	Suffocation
	Drowning
6 months	
	Falls
	Burns
	Medicine poisoning
	Drowning
	Toy hazards
9 months	
	Concussion
	Drowning
	Driving hazards
	Finger pinching
12 months	
	Poisoning
	Falls
	Sunburn
	Driving hazards
18 months	
	Poisoning
	Falls
	Sunburn
	Driving hazards

The value of using a behavioral approach to design an injury prevention program is widely recognized by researchers [24,25]. The Theory of Planned Behavior is a model that links beliefs and behavior to predict people’s intention to perform actual behaviors [26]. This intention comprises three important elements: attitude, subjective norms, and perceived behavioral control. Attitudes are derived from a person’s perceptions about the consequences of behavior and the importance of these consequences to the individual. Subjective norms are derived from one’s perception of beliefs about significant others’ preferences and the individual’s motivation to comply with their wishes. Perceived behavioral control is derived from a person’s perception of the difficulty to conduct the behavior. Adriaensens et al reported that an online intervention was able to deliver a positive effect on knowledge, attitudes, intentions, and actual injury-preventive behavior [27]. Therefore, besides being a knowledge hub, the intervention website and mobile app will incorporate additional feedback counseling, online consultations, a discussion forum, interactive games, and video demonstrations to improve participant’s attitudes, intentions, and perceived behavioral control toward home safety practices.

Mothers can use the discussion forum to exchange opinions or ideas related to domestic safety, such as the usefulness of safety gadgets, uncommon domestic injury hazards, and home safety emergency plans. Concerned mothers can also use the forum for online consultation by asking questions about childhood injury, and can even upload photos, which will then be answered by safety experts. However, in an emergency, participants should contact emergency services and attend their nearest accident and emergency department. The forum can serve as a practical learning platform and provide parents or caregivers with additional social value through online interaction. Online discussion forums have been shown to enhance social support and the feeling of parental efficacy, and thus can improve one’s attitudes and intentions to adopt safer practices [18].

Additional interactive elements such as video demonstrations, games, and quizzes will be added to the website and mobile app. Two interactive games have been designed to deliver key information related to childhood safety and injury prevention. In the first game (named *spot the difference*), players need to identify differences in potential home hazards between two pictures. Explanations will be provided when players spot the potential home hazard, such as the type of injury (eg, scald and poisoning) that the hazard would cause. In the second game (named *cue and action*), players need to select a particular prevention tool to stop the potential hazard that may cause domestic injury. These interactive games and video demonstrations would help the participant create mnemonics for injury prevention, and enhance one’s perceived behavioral control toward home safety practices. Safety practice demonstrations by health care providers who are role models and influencers have been reported to be useful in engaging mothers and reinforcing positive outcomes [6,7].

The website will contain comprehensive injury prevention information and useful links and telephone numbers. All information contained in the website and the app will be consolidated and updated regularly, taking into account the changing patterns arising from local injury profiles, caregivers’ responses, and the physical environment. Reference and guidance materials such as injury-related publications of evidence-based good practices, statistical data, and frequently asked questions will be made available on the website to reinforce users’ perceived behavior control toward domestic injury prevention. In addition, the injury profiles of the 18 districts in Hong Kong, with infographic summaries, will be uploaded to the website for reference [3].

### Technology

The existing CIPRA website will be redesigned to accommodate the intervention program in this study, and will be cohosted by CIPRA and the authors’ department. A mobile app will be made available for downloaded on Android phones and iPhones. The website will run on a Linux server located and managed under the authors’ department, and will have regular backups to prevent any accidental data loss.

### Measures

This study aims to increase mothers’ knowledge of child domestic safety, and to improve their attitudes, intentions, perceived behavioral control, and actual behavior related to home safety practice. The following five evaluation components will be included to demonstrate the effectiveness of the technology-based intervention: general safety knowledge, age-appropriate safety questionnaire, injury prevention behavior checklist, website and mobile app usage statistics, and website and mobile app user acceptance.

#### General Safety Knowledge

This component aims to evaluate changes in mothers’ general knowledge related to domestic injury prevention [28,29]. The items in the questionnaire are in a statement format and cover two key topics: (1) common childhood domestic injuries, and (2) safety precautions (see Multimedia Appendix 1).

#### Age-Appropriate Safety Questionnaire

This component examines age-appropriate domestic safety knowledge, attitudes, intentions, and perceived behavioral control toward home safety practice (Table 1) [30-32]. The multiple-choice questions in the questionnaire are categorized into two sections: (1) age-specific questions, and (2) assessment questions that were answered incorrectly in the previous stage by the participant (see Multimedia Appendix 2). This targeted component is designed to reinforce safety concepts and sustain knowledge enhancement.

#### Injury Prevention Behavior Checklist

This component examines different age-appropriate injury prevention behaviors. The injury prevention behavior checklist serves as a behavioral measure for: (1) identifying hazards, and (2) implementing safety measures in a home environment (see Multimedia Appendix 3).

#### Website and Mobile App Usage Statistics

Participants will be required to register online as a *user* to access the website and the mobile app. By logging into the system, we will be able to record all actions taken by each user, including login time, duration of website usage, and what information was accessed. The captured data can be further analyzed and used for the purpose of incentive reimbursement.

#### Website and Mobile App User Acceptance

Towards the end of the intervention period, subjects will be reminded to complete a user acceptance evaluation (see Multimedia Appendix 4). The practicability of the technology-based domestic injury prevention website and mobile app will be evaluated in terms of its layout, structure, usability, readability, accessibility, and ease of navigation [33].

### Incentives

To enhance participation and minimize attrition in the follow-up months, incentives will be given to mothers who continue to complete evaluations. Proposed incentives include safety gadgets and cash coupons (valued at Hong Kong $50; approximately US $6.40) from companies that promote child domestic safety.

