## Methods

### Study Design

This study will be a randomized controlled trial of the effectiveness of a technology-based injury prevention program for enhancing mothers’ knowledge of child safety (Figure 1). Mothers will be recruited from the antenatal clinics and postnatal wards of two major public hospitals in Hong Kong: Kwong Wah Hospital and Queen Mary Hospital. Between October, 2016 and January, 2017, nurses will identify potential participants. An experienced research assistant will provide the participants with an information sheet explaining the study, along with a consent form. The inclusion criteria will include mothers attending the antenatal clinics or staying in the postnatal wards at Kwong Wah Hospital or Queen Mary Hospital. The exclusion criteria will include subjects unable to read Chinese, and those without Internet access.

Participants will be randomly allocated into the intervention and control groups in a 1:1 ratio. All participants will be given an information pack consisting of a parenting booklet from the Maternal and Child Health Centers (MCHC). This booklet is publicly available and provides brief and general home safety tips for mothers with children under 3 years of age. The intervention group will also be given an additional leaflet containing a brief introduction to the Internet-based domestic safety platform, and instructions on how to access the website. Mothers can easily access this practical online parenting resource through the website or a mobile app. The online resource contains information on various safety topics and educational materials, including general and age-appropriate injury prevention measures suitable for mothers with infants and children between 2 and 18 months of age. Participants in the intervention group will be periodically contacted by telephone and electronic messaging to encourage them to access and engage with the domestic safety website. The research team will provide technical support to all participants who encounter problems accessing the intervention website or mobile app. Apart from technical support, no other intervention will be provided to those accessing the website or mobile app by any therapist, nurse, care provider, or physician. The control group will receive only the MCHC parenting booklet.

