### Randomization and Masking

Participants will be randomly assigned to the intervention group or the control group by stratified randomization within each hospital, using random numbers generated using R Statistical Software. Each participant will receive a sealed opaque envelope assigning them to either the intervention (website and mobile app access) or the control (no website or mobile app access) groups. The participant recruitment and randomization process will be independently carried out by different research assistants. Outcome assessors will be blinded to the allocation of participants in each group.

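### Safety gadgets proposed as retention incentives can change the home-safety behaviour outcome, and the usage section leaves room for a reward that only the intervention arm could earn

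*Protocol article*

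**What the plan says.** The Incentives section sets the condition: "incentives will be given to mothers who continue to complete evaluations". It names no arm. It then lists the rewards: "Proposed incentives include safety gadgets and cash coupons". The coupons are worth HK$50 and come from companies that promote child domestic safety. The stated purpose is to limit attrition in the follow-up months.

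The Injury Prevention Behavior Checklist section describes a measure with two parts, hazard identification and "implementing safety measures in a home environment". The Abstract lists self-reported home safety behaviour among the secondary outcomes. Study Design places the age-specific assessments at 2, 6, 9, 12 and 18 months. Data Analysis compares behaviour between arms by independent-sample t-test.

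The Website and Mobile App Usage Statistics section says that every action of a registered user is logged, "including login time, duration of website usage, and what information was accessed". It continues: "The captured data can be further analyzed and used for the purpose of incentive reimbursement". Randomization and Masking describes "the control (no website or mobile app access) groups", and Study Design adds: "The control group will receive only the MCHC parenting booklet". Data Analysis correlates the outcome measures with platform usage to examine dose-response.

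**The concern.** Two features of the plan need separating.

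First, the reward overlaps with what is measured. The Introduction itself names the use of child safety devices at home as one way in which parents reduce risk. A free safety gadget supplies part of the behaviour that the programme is meant to teach and that the checklist scores. Because the assessments repeat, a gadget given for one of them can affect those that follow.

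Second, two sections describe the basis for incentives differently. One rewards completing evaluations. The other permits logged platform use to feed into reimbursement. Only the intervention arm can produce such logs. If that permission were used as a payment rule, part of any behaviour difference between arms could come from gadgets and not from the programme. Mothers in one arm would also have an extra reason to stay in the study, and usage would partly reflect response to payment.

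**Working it through.** No figure in the plan quantifies this point, so the main check is to set the sections side by side. A short illustration on assumed values follows.

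**Who can receive what**

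| Reading | Basis for reward | Intervention arm | Control arm | Main consequence |
|---|---|---|---|---|
| Incentives section as written | Completing evaluations | Eligible | Eligible | Possible dilution of the behaviour contrast |
| Usage clause, if made a payment rule | Logged platform use | Eligible | Cannot qualify | Unequal receipt and retention; the exposure is rewarded |
| Usage clause, if only a completion check | Completing evaluations | Eligible | Eligible | As in the first row |

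**Equal receipt.** If a gadget adds the same amount to every mother's score, the contrast is unchanged. Dilution arises where the gadget secures an item that intervention mothers would have met anyway. Suppose an item is met without gadgets by proportions pI and pC in the two arms, and a gadget converts a fraction f of the mothers who would not have met it. Then

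- intervention: pI + f(1 − pI)
- control: pC + f(1 − pC)
- difference: (1 − f)(pI − pC)

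The contrast on that item shrinks by the fraction f, for example by 10%, 25% or 50% at f = 0.1, 0.25 or 0.5. These values of f are assumptions. The documents do not say which gadgets are meant, so f cannot be estimated.

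**Unequal receipt.** The Sample Size Calculation section gives 92 evaluable mothers, which its inflation implies is per arm: 92 / (1 − 0.40) = 153.3, rounded up to 154 per arm, and 2 × 154 = 308. Let gadget receipt differ between arms by a share p, let a gadget raise the behaviour score by g SD, and let the programme have no true effect on behaviour. Then

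- spurious difference: b = p × g
- standard error in SD units: √(2/92) = 0.147
- two-sided rejection rate: Φ(b/0.147 − 1.96) + Φ(−b/0.147 − 1.96)

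| p (assumed) | g in SD (assumed) | b | Rejection rate at nominal 5% |
|---|---|---|---|
| 0 | any | 0 | 0.050 |
| 0.25 | 0.2 | 0.05 | 0.063 |
| 0.5 | 0.2 | 0.10 | 0.104 |
| 0.5 | 0.3 | 0.15 | 0.174 |
| 1 | 0.2 | 0.20 | 0.274 |

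The first row is the case of equal receipt: no false-positive inflation. The last row needs every intervention mother and no control to receive a gadget, which the Incentives section does not say. The table shows direction and scale only.

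**Dose-response.** Usage exists only in the intervention arm, so the correlation is not protected by randomisation in any case. Paying for use would add two problems. Usage would partly measure response to the reward, and heavier users could receive more gadgets, which would link usage to the checklist score by a path outside the programme content.

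**The case against.** The strongest reply is that the usage clause is permissive. It says what the logs can be used for and sets no threshold or payment rule. It may mean only that the log serves to confirm that questionnaires were completed, since Study Design describes online feedback prompted by questionnaire answers. On that reading the two sections agree. The named data items (login time, duration, information accessed) fit a completion check less well, but the reading cannot be excluded.

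The Incentives section restricts nothing by arm, and controls are contacted on the same schedule as the intervention arm to complete questionnaires. The sentence giving controls the booklet alone most naturally refers to educational material, not to incentives. A reader might infer that the plan pays only the intervention arm. The documents do not say so.

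A reader might also try to size the effect by assuming a checklist SD of 2 to 3 items. One extra item would then equal 1/3 = 0.33 to 1/2 = 0.50 SD, close to the planning effect of 0.42. That comparison does not hold. The SD and the one-item gain are both assumed, the figure applies to recipients and is not a difference between arms, and 0.42 is an effect on knowledge, not on behaviour.

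Finally, the incentives are only proposed, and an article may leave gadget type, timing and quantity to the full protocol. That is accepted for those details. What stands is what the article does state: safety items as rewards during follow-up, a checklist that scores safety measures in the home, and a usage clause not reconciled with the completion rule.

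**Conclusion.** The point holds as a design weakness worth correcting, limited to the secondary behaviour outcome and the dose-response analysis. Under the incentive rule as written, the expected consequence is dilution, which works against finding an effect. Bias between arms requires unequal receipt, through a usage-based reward or through unequal completion. The first of these is allowed by the text but not mandated.

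Gadgets do not act directly on the primary outcome, the change in safety knowledge. An incentive favouring one arm could reach it only indirectly, through unequal retention in a trial that already expects 40% attrition. The sample size is unaffected.

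The size of the effect cannot be derived from the documents. That a gadget would move the checklist score is an inference from what the checklist measures, since neither the type of gadget nor the individual items appear in the article text.

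**What to change.** - State one incentive rule in the Incentives section, identical in both arms and tied only to completing evaluations.
- During follow-up, give coupons of the same value that are not tied to safety products. If gadgets are wanted, give them to both arms after the 18-month questionnaires.
- In Website and Mobile App Usage Statistics, delete the words "used for the purpose of incentive reimbursement", or limit them to verifying that questionnaires were completed.

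If gadgets must stay in the follow-up period, stating that receipt is identical in both arms and recording it by arm would address the risk of bias, but not the dilution.

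The cost is small: a change of wording, no change in sample size, and no change in the coupon value. The downside is that donated safety items cannot serve as incentives until follow-up ends.

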### Data Analysis

Changes in participants’ knowledge of child safety will be studied by comparing their knowledge before and after completing the injury prevention program, and by comparing the participants’ knowledge of child safety in the intervention and control groups. Regression analysis will be used to examine the intervention effectiveness, adjusted for participant demographics (eg, gender, age, and socioeconomic status of the parent). Data will be analyzed by an intent-to-treat approach to address loss of any follow-up data. Independent sample t-tests will be used to examine the between-group differences in age-appropriate safety knowledge, attitudes, intentions, perceived behavioral control, and actual behavior related to home safety practice. Dose-response relationships between the outcome measures and the website and mobile app usage will be determined by correlation analysis. Website and mobile app usage data will be summarized based on the number of users and their time spent using these resources during the entire intervention period. A summary of the user acceptance evaluation will be compiled to improve and develop the website and mobile app.

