### Sample Size Calculation

With reference to a computer-based parenting intervention for child injury prevention that reported a small to medium effect (d=0.42) for knowledge change [21], 92 subjects will be needed for this intervention study to detect an effect with 80% power and a 5% significance level. Assuming a 40% attrition rate between preevaluation and postevaluation, at least 154 participants should be recruited to each of the intervention and control groups.

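### The effectiveness regression does not name baseline knowledge or hospital as covariates and lists gender, a constant among mothers; the before-after comparison is not marked as descriptive

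*Protocol article*

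**What the plan says.** The Abstract makes the change in the mother's child safety knowledge the primary outcome. Under Study Design, general safety knowledge is measured at the antenatal clinic or postnatal ward and again when the child is 18 months old.

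The Data Analysis section gives two ways of studying this outcome. One is "comparing their knowledge before and after completing the injury prevention program"; the other compares the intervention and control groups. It then names the model: "Regression analysis will be used to examine the intervention effectiveness, adjusted for participant demographics (eg, gender, age, and socioeconomic status of the parent"). The same section says that the analysis will be by intent-to-treat.

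Three other statements bear on the point:
- Randomization and Masking: allocation is by "stratified randomization within each hospital".
- Study Design: "Mothers will be recruited from the antenatal clinics and postnatal wards of two major public hospitals in Hong Kong".
- Sample Size Calculation: the reference study "reported a small to medium effect (d=0.42) for knowledge change", and "92 subjects will be needed for this intervention study to detect an effect with 80% power and a 5% significance level".

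**The concern.** Three things in the Data Analysis section fit the design badly.

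1. **Covariates.** The adjustment set is described as demographics. The baseline knowledge score is likely to be among the strongest predictors of the 18-month score, and hospital is the factor on which randomisation is stratified. Neither is a demographic, so neither falls naturally under the examples given. At stake is precision that the trial could have at no cost.

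2. **Gender.** It is the first adjuster listed, yet it takes a single value in a sample of mothers.

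3. **Before-after comparison.** It stands beside the between-arm comparison with no statement that only the latter bears on effectiveness. Both arms receive a booklet with home safety tips, both complete safety questionnaires at several child ages, and all mothers gain experience over the period. Knowledge could rise without any effect of the program, and a reader of the results could take that rise as evidence for it.

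**Working it through.** **Inputs.** d = 0.42, 80% power, 5% significance (taken as two-sided), 92 evaluable, 40% attrition and 154 recruited per arm, all from Sample Size Calculation. The 92 is read as per arm, because 154 × 0.60 = 92.4. The correlation r between baseline and 18-month score is not given; 0.3 to 0.7 is assumed.

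**The plan's own figure.** Normal approximation: n = 2 × ((1.960 + 0.842)/0.42)² = 88.99, so 89 per arm. The t-based calculation gives 89.96, so 90. The stated 92 is within 2 of that. Attrition: 92/0.60 = 153.3, so 154 per arm and 308 in total. The sample size reproduces. Power at 92 per arm is 81.3% (normal) or 80.9% (t).

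**Baseline as covariate against a change score.** With equal variance σ² at both times:
- change score: 2σ²(1 − r)
- baseline as covariate: σ²(1 − r²)
- ratio: (1 + r)/2

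If 0.42 is on the change-score SD, the effective standardised difference is 0.42/√((1+r)/2), and power is Φ(effective d × √(92/2) − 1.960), with √46 = 6.782. The remaining demographics are taken to explain nothing.

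| r (assumed) | Variance ratio | Effective d | Power, change score | Power, baseline as covariate | n per arm for 80% |
|---|---|---|---|---|---|
| 0.3 | 0.65 | 0.521 | 81.3% | 94.2% | 58 |
| 0.5 | 0.75 | 0.485 | 81.3% | 90.8% | 67 |
| 0.7 | 0.85 | 0.456 | 81.3% | 87.1% | 76 |

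The article does not say which SD scales d. If 0.42 is on the final-score SD instead, power at r = 0.3, 0.5 and 0.7 is 67.3%, 81.3% and 95.7% for a change score, against 84.8%, 90.8% and 97.9% with baseline as covariate. The covariate analysis is ahead on either scale throughout this range.

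**Hospital left out.** If hospital explains a share R of the outcome variance and stratification balances the arms within hospital, the unadjusted standard error is too large by 1/√(1 − R). The actual two-sided level is then 2 × (1 − Φ(1.960/√(1 − R))): about 0.049, 0.044 and 0.039 for assumed R = 1%, 5% and 10%. The arm estimate stays unbiased.

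**Gender.** A constant column is collinear with the intercept. A test design matrix with intercept, arm, constant gender and one continuous covariate has rank 3 of 4 columns, so a gender coefficient cannot be estimated.

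**Before-after gain with no program effect.** Suppose a paired t-test were run in one arm of 92, with a general gain of 0.1, 0.2, 0.3 or 0.4 SD of change and no effect of the program. It would reach p < 0.05 in about 16%, 48%, 81% or 97% of trials. Both the gains and the test are assumptions; the article names no before-after test.

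**The case against.** The strongest reply is that this is a condensed article. Its covariates are only examples, and the full list could stand in an analysis plan that is not shown. That has force: nothing in the text excludes baseline or hospital, which makes the covariate part the weakest of the three. It does not remove the part, because the article names a class, demographics, to which neither variable belongs. Nor does it excuse gender, which no fuller document can make usable here.

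Some stronger readings are tempting, and the document does not support them:

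- **That baseline is ignored.** The primary outcome is a change, and the sample size rests on an effect for knowledge change. Baseline enters through the difference; it is only not named as a covariate.
- **That the arm comparison is biased or the trial underpowered.** Neither follows. Leaving out baseline or hospital costs precision, and the planned power reproduces without them.
- **That the before-after comparison is the primary analysis.** It is mentioned first, but order is not priority, and the section assigns effectiveness to the regression. What is missing is a plain statement that the before-after comparison is descriptive.
- **That the wording about completing the program contradicts intent-to-treat.** With 40% attrition assumed, it could be read as a restriction to completers. It can equally mark the timing of the second measurement. This is an ambiguity to clear up.

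Recruitment setting (antenatal or postnatal) is also unnamed and alters the interval from baseline to 18 months. It is not a stratification factor, and the article gives no gestational age at enrolment from which to size its effect, so it is an optional covariate only.

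**Conclusion.** The point holds as a worthwhile improvement to the stated analysis. No figure in the article is wrong on this account.

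- **Baseline:** used as a covariate in place of a plain change score, it takes power from about 81% to between 87% and 94% for r from 0.7 down to 0.3. This assumes d = 0.42 on the change-score SD, 92 evaluable per arm and equal variances at both times.
- **Hospital:** leaving it out costs slight conservatism, with an actual level of about 0.049 to 0.039 if hospital explains 1% to 10% of the variance.
- **Gender:** a definite slip, with no numerical consequence.
- **Before-after comparison:** an unguarded statement. Randomisation does not protect it, and it should not be left open to being read as evidence of effectiveness.

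**What to change.** In the Data Analysis section:

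1. Name one primary analysis: linear regression of the 18-month general safety knowledge score on arm, baseline general safety knowledge score, hospital, age and socioeconomic status. The arm coefficient is the test of effectiveness. Putting the change score on the left with the same covariates gives the same arm coefficient, so the primary outcome need not be redefined.
2. Delete gender.
3. Report before-after changes within each arm as description, without a test.
4. State that the measurement after the program is the 18-month assessment, whether or not the mother completed the program, in line with intent-to-treat.
5. Optionally, add recruitment setting as a covariate.

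The cost is wording only. The baseline score is already collected, hospital is known from randomisation, and age and socioeconomic status are already listed as adjusters. Recruitment setting should be known at enrolment, although the article does not say that it is recorded for analysis. The sample size can stay as it is.
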